### Interim analyses {21b}

No intermediate analyses are carried out.

### Methods for additional analyses (e.g. subgroup analyses) {20b}

In the following, supplementary analyses for the primary estimand are described: The same test as in the primary analysis will be conducted in the per-protocol set (PP, based on those patients without major protocol violation) and the as-treated set (AS, considers those subjects who have actually received the intervention, analysed in the group they were treated). Failure to respect the exclusion criteria or to follow the technical aspects of the assigned study group (suture material, stitch technique, used mesh) will be considered as major protocol violations. Analyses in the PP and AS set are known to be biased and do not correspond to any estimand and thus have to be interpreted with great caution. In addition, the primary endpoint will be compared between the study groups by the Mann-Whitney *U* test. In contrast to the primary endpoint model, the Mann-Whitney *U* test does not consider the mean CCI, but the “distribution of the values per se” and therefore does not address the primary estimand.

Pre-specified subgroup analysis will be performed in the following subgroups based on the mITT:Patients who switched from MIN-E to HYBRID-E (y/n)Patients with a tumour of the thoracic oesophagus versus a tumour of the oesophagogastric junctionSquamous cell versus adenocarcinomaRobot-assisted procedures versus conventional minimally invasive proceduresAdherence to ERAS items (yes/no)Neoadjuvant therapy (y/n)Further subgroups will be determined in the statistical analysis plan

In general, for the mITT, all baseline values will be evaluated descriptively per group and for the whole cohort. Furthermore, secondary endpoints will be evaluated descriptively and effect sizes will be reported together with 95% confidence intervals for the corresponding effects. In addition, regression models including the treatment group as the fixed effect and centre as random effect as specified for the primary endpoint will be used. Time-to-event endpoints will be evaluated by methods of survival analysis comprising the Kaplan-Meier method and Cox proportional hazards models. Secondary endpoint analysis will be performed on the mITT and the AS and no missing values will be imputed.

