### Intervention description {11a}

#### Experimental and control intervention

In the experimental group, both the abdominal and thoracic phases of the elective oesophagectomy will be performed minimally invasively, i.e. as total minimally invasive oesophagectomy (MIN-E). MIN-E can be performed either via “classical” minimally invasive laparoscopy and thoracoscopy or via robotic-assisted minimally invasive oesophagectomy (RAMIE) or any combination of the two. A recent international consensus study has developed an operation manual for oesophagectomy [21]. The following steps are an adaptation of this consensus and serve as an operation recommendation for both the experimental and control interventions. Surgeons in the MICkey trial may deviate from this manual and should perform the procedure according to their local standard, i.e. according to the technique in which the operating surgeon has reached the plateau of her/his learning curve. In the following, the lymph node sections are named according to the Japan Esophageal Society and Japanese Gastric Cancer Association.

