##### Step IV: Thoracic anastomosis

Perform an oesophagogastrostomy using your preferred method (stapler or suture).

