##### Step V: Surgical adjuncts and closure

A nasogastric or nasojejunal tube may be placed. Thoracic drain(s) may be placed prior to the closure of the thoracic incision. After confirmation of haemostasis, the lung must be re-inflated under direct vision. Closure of the chest should be performed according to the local standard.

In the control group, the elective oesophagectomy will be performed as HYBRID-E, i.e. the abdominal phase of the operation will be performed minimally invasively while the thoracic part will be performed as open surgery (via a thoracotomy). The essential surgical steps performed in the control intervention are the same as for the experimental intervention and are outlined above.

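### The technical part of the per-protocol definition lists suture, stitch and mesh, which no study group is assigned, so the set cannot reflect adherence to MIN-E or HYBRID-E

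*Protocol article*

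**What the plan says.** Section {20b} repeats the primary test in a "per-protocol set (PP, based on those patients without major protocol violation"). It names two kinds of major violation. The first is a breach of the exclusion criteria. The second is a failure "to follow the technical aspects of the assigned study group (suture material, stitch technique, used mesh) will be considered as major protocol violations".

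The intervention description says what is allocated. For MIN-E, "both the abdominal and thoracic phases of the elective oesophagectomy will be performed minimally invasively". For HYBRID-E, "the abdominal phase of the operation will be performed minimally invasively while the thoracic part will be performed as open surgery (via a thoracotomy"). Everything else is common to the arms: "The essential surgical steps performed in the control intervention are the same as for the experimental intervention and are outlined above".

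The common steps are not binding: "Surgeons in the MICkey trial may deviate from this manual and should perform the procedure according to their local standard". For the anastomosis the text reads "Perform an oesophagogastrostomy using your preferred method (stapler or suture"). Oversewing of the conduit staple line (Step 5) is optional, and chest closure (Step V) follows local practice.

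**The concern.** A per-protocol analysis of a surgical comparison should set aside patients who did not receive the operation they were allocated. Here the examples that define technical non-adherence are details that the trial neither allocates nor standardises. The feature that separates the arms, open or minimally invasive chest access, is not listed. Nor is receipt of an Ivor-Lewis resection.

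This is not a detail left for the statistical analysis plan. The article states specific criteria, and they do not fit the trial. An analysis plan that follows them inherits the error, and one that departs from them contradicts the protocol. What is at stake is whether the per-protocol result says anything about adherence that the mITT result does not.

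**Working it through.** **Listed items against what is assigned**

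- *Suture material:* not assigned. Stapler or suture is the surgeon's choice (Step IV), and oversewing is by centre standard (Step 5).
- *Stitch technique:* not assigned, for the same reasons. Chest closure is also local (Step V).
- *Mesh:* appears in no surgical step and nowhere else in the article.
- *Thoracic access:* assigned, and the only difference between the arms. Not listed.
- *Type of resection:* Ivor-Lewis in both arms. Section {11b} foresees other operations and keeps those patients in the trial. Not listed.

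**What the literal rule yields**

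1. No arm has an assigned suture, stitch or mesh, so no patient can fail to follow one. The technical rule removes nobody.
2. The exclusion-criteria rule still works. Assuming the per-protocol set is drawn from the mITT set, it equals the mITT set minus exclusion-criteria violators.
3. Section {11b} places converted patients in the mITT population, and {20a} analyses them as randomised. They therefore stay in the per-protocol set under that arm. So does any patient in the mITT set who had another type of oesophagectomy.

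**How many patients**

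Inputs: conversion below 5% in each group (section {11b}); 76 randomised per group and 10% intraoperative drop-out (section {14}).

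- Upper bound on all randomised patients: 0.05 × 76 = 3.8 per arm.
- Upper bound on resected patients, the mITT base: 76 × 0.90 = 68.4, and 0.05 × 68.4 = 3.4 per arm.

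So at most about 3 to 4 converted patients per arm. The article gives no rate for non-Ivor-Lewis resections or for HYBRID-E operations completed thoracoscopically, so these cannot be counted.

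**Which conversions are possible in each arm**

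Conversion covers the abdominal or the thoracic part (sections {11b} and Surgical outcome measures). In HYBRID-E the chest is open by design, so every conversion there is abdominal. In MIN-E it can be either. A rule on thoracic access alone would therefore miss every HYBRID-E conversion and the abdominal ones in MIN-E.

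**Sample size, for context**

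A two-sided t-test with a difference of 10, SD 20, α = 0.05 and 80% power needs 63.8, hence 64 per group, as stated. Then 128/0.85 = 150.6, rounded up to 151, and to 152 for equal groups, also as stated. The per-protocol definition plays no part in these figures.

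**The case against.** The strongest defence has four parts.

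- *Status.* The per-protocol analysis is supplementary. Section {20b} itself calls it biased and tied to no estimand. The confirmatory test uses the mITT set, and secondary endpoints use the mITT and as-treated sets. This stands, and it limits the severity.
- *Other analyses cover crossover.* The as-treated analysis regroups patients by operation received, and a subgroup for switching from MIN-E to HYBRID-E is pre-specified. This stands in part. Regrouping is not the same as removing violators, and neither analysis repairs the per-protocol rule.
- *The general words could carry the rule.* If the bracket is treated as misplaced examples, the words before it, "Failure to respect the exclusion criteria or to follow the technical aspects of the assigned study group", could be taken to mean thoracic access. That is possible, but the text does not say so, and two analysts could build different sets.
- *Excluding conversions is a choice.* The protocol regards a few conversions as part of clinical reality, and thoracic conversion can happen only in MIN-E. This is a fair reason to require an explicit classification. It is no reason to keep the bracket.

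A reader might infer more than the documents support:

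- *That the per-protocol analysis is meaningless.* It is not, because the exclusion-criteria rule still operates.
- *That violations will be decided after outcome data are seen.* Section {17a} requires the analysis plan to be finished before database closure, and {20a} closes the database before the primary analysis.
- *That up to 8 MIN-E patients are affected.* The Fig. 1 caption mentions 8 converted patients, but for the as-treated set and for a figure not shown. It moves only 4 of them to HYBRID-E, and 8/76 = 10.5% conflicts with the expected rate below 5%. It is not a usable bound.
- *That the bracket was carried over from another kind of operation.* This is plausible for mesh but remains inference. Suture and stitch could describe a hand-sewn anastomosis; they are simply not assigned.

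**Conclusion.** The point holds in a limited form. The technical criteria conflict with the intervention description and can exclude nobody if applied as written. The supplementary per-protocol analysis then differs from the mITT analysis only by exclusion-criteria violators and does not reflect adherence to the allocated approach.

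The size rests on the protocol's own conversion expectation, used as an upper bound, and on the assumption that the per-protocol set is a subset of the mITT set. The non-Ivor-Lewis component is unknown. No primary conclusion, error rate or sample size depends on the definition. It should be fixed before the analysis is run, but it does not threaten the trial.

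**What to change.** Replace the bracket in section {20b} so that technical major violations are:

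1. an operative approach completed other than allocated, defined by thoracic access, with an explicit statement of how abdominal conversions are classified in both arms; and
2. a resection other than the abdominal and right-thoracic Ivor-Lewis procedure.

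Keep breach of the eligibility criteria as the other kind of violation. State that the classification of patients is settled before database closure without sight of the CCI.

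This costs a sentence or two in the protocol, mirrored in the analysis plan. It changes only an analysis set, not the conduct of surgery. Conversions and their reasons are already recorded in the eCRF. The downside is that thoracic conversion can occur only in MIN-E, so exclusions may be unequal between arms. The existing caution about bias in the per-protocol set already covers this and should stay.

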If another type of surgery (other than abdominal and right thoracic oesophagectomy, Ivor-Lewis procedure) is indicated for complete tumour resection (e.g. transhiatal extended gastrectomy or abdomino-cervical oesophagectomy), the patient remains in the trial and will be followed up for the entire trial period. This is meaningful, because these types of surgeries constitute major operations, are associated with major complications and oncological outcome parameters can be analysed. The MICkey trial randomization will occur preoperatively, as intraoperative randomization is impractical due to the need for different operative set-ups (e.g. preparation of robot/laparoscopic towers) and patient preparation. To minimize bias, two intraoperative exclusion criteria have been defined. As a consequence, intraoperative exclusion of previously randomized patients might occur:*Case 1 (intraoperative diagnosis of previously occult metastases that prohibit surgical resection according to current S3 guidelines)* [19]: In this case, patients in both groups will undergo diagnostic laparoscopy only, as the abdominal part of the operation is the same in both groups and will be performed minimally invasive in both groups. Diagnostic laparoscopy is a minor surgery, with very few associated complications. Consequently, follow-up for the primary endpoint (comprehensive complication index) makes no sense, as it adds nothing to answering the primary research question, namely which surgical technique is associated with less complications after oesophagectomy, an operation which is associated with major complications. In addition, almost all secondary endpoints are meaningless in patients undergoing diagnostic laparoscopy only. Therefore, these patients will be excluded from the study. These patients will be defined as “intraoperative drop-out”. However, in line with the current S3 guidelines [19], patients with newly diagnosed intraoperative “sehr limitierter Fernmetastasen” (very limited metastases), which are “gut resektabel” (easily resectable), oesophagectomy in combination with resection of this “kleine, gut resektable Metastase” (small, well-resectable metastasis) should be performed [9] (recommendation 8.13). In this case, the patient remains in the trial and is regularly followed up.*Case 2 (tumour resection technically impossible)*. As for case 1, follow-up of patients makes little sense as these patients will undergo minor surgery only and DFS cannot be measured. Again, these patients will be defined as “intraoperative drop-outs”.The occurrence of both cases (case 1 and case 2) is assumed to be equally distributed between both study groups.

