### Relevant concomitant care permitted or prohibited during the trial {11d}

Additional treatments including all perioperative procedures are performed according to institutional standards and will be recorded to adjust for possible confounders in both groups.

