## Statistical methods

### Statistical methods for primary and secondary outcomes {20a}

For the examination of the primary endpoint, CCI within 30 days after surgery, the hypotheses to be assessed in the primary analysis are as follows:

H0: μ1 = μ2 vs H1: μ1 ≠ μ2, where μ1 and μ2 denote the mean CCI in the control and intervention groups respectively.

The confirmatory analysis of the primary efficacy endpoint corresponds to the primary estimand. Only patients who underwent oesophagectomy will be included in the primary analysis (drop-out assumed to be less than 10%) and they will be analysed in the group they were randomized (converted patients remain in their group). This reflects an analysis according to a modified intention-to-treat principle and the derived dataset is referred to as the mITT. The level of significance is set to 5% (two-sided).

The mean differences of the CCI will be examined using a linear mixed model including treatment group and adjusting for age as a fixed effect, as well as center as a random effect. Due to the stratified randomization and relatively large number of centers in relation to the sample size, inclusion of centre as a random effect is recommended [24]. The correlation matrix will have a variance components structure. The primary analysis will be performed after data for the primary endpoint is available for all patients. The database will be closed before the analysis of the primary endpoint.

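### Two of the pre-specified mITT subgroups, switching from MIN-E to HYBRID-E and ERAS adherence, are not baseline factors, and the switch subgroup has no control patients at its yes level

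*Protocol article*

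**What the plan says.** Section {20b} of the protocol article introduces its list with "Pre-specified subgroup analysis will be performed in the following subgroups based on the mITT". Six subgroups follow. Three are baseline factors: tumour site, histology and neoadjuvant therapy. The other three are "Patients who switched from MIN-E to HYBRID-E (y/n", robot-assisted versus conventional minimally invasive surgery, and adherence to ERAS items. The SAP is mentioned only as the place for further subgroups, so the protocol itself fixes these six.

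Four other statements matter here.

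- **Control operation** (Intervention description {11a}, Step V): "the abdominal phase of the operation will be performed minimally invasively while the thoracic part will be performed as open surgery".
- **Analysis set** ({20a}): for the mITT, "they will be analysed in the group they were randomized (converted patients remain in their group".
- **Timing** ({11b}): randomisation is preoperative because "intraoperative randomization is impractical due to the need for different operative set-ups (e.g. preparation of robot/laparoscopic towers". Centre is the only stratification factor ({16a}).
- **Platform** ({11a}): "MIN-E can be performed either via “classical” minimally invasive laparoscopy and thoracoscopy or via robotic-assisted minimally invasive oesophagectomy (RAMIE) or any combination of the two".

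Section {20b} warns that the per-protocol and as-treated analyses are biased and match no estimand. It gives no such warning for the subgroups. Section {11d} says that concomitant treatments and perioperative procedures "will be recorded to adjust for possible confounders in both groups".

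**The concern.** A subgroup analysis of a randomised comparison keeps the protection of randomisation only if the subgroup is defined by something that allocation cannot influence. Switching and ERAS adherence do not meet this condition, yet they stand beside true baseline factors under the same pre-specified label.

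Switching is the clearer case. It is an intraoperative event that exists in one arm only, and {11b} names technical difficulties and bleeding as reasons for conversion. Removing such patients from MIN-E alone, while their counterparts stay in HYBRID-E, breaks the comparability of the arms in much the way the protocol criticises for the per-protocol and as-treated sets.

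At stake is how the secondary report is read. A contrast among patients who did not switch could be presented as pre-specified randomised evidence for MIN-E when part of it is selection.

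**Working it through.** **The plan's own figures.** No figure is stated for any subgroup. The sample size, which is not in dispute, reproduces: with a difference of 10, SD 20 and two-sided alpha 0.05, a t-test with 64 per group has 80.1% power, and 64 / 0.85 = 75.3 rounds up to 76 per group, or 152.

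**Switch = yes.** Code arm A (0 = HYBRID-E, 1 = MIN-E) and switch S. A HYBRID-E patient cannot switch from MIN-E, so S = 1 implies A = 1.

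| | HYBRID-E | MIN-E |
|---|---|---|
| Switched | 0 | about 3 (5% × 64 = 3.2) |
| Not switched | all | the rest |

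Because A × S = S for every patient, the design matrix [1, A, S, A × S] has rank 3, not 4. Neither the treatment effect at the yes level nor the interaction is identified. This needs no assumption and does not depend on the number of switchers.

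**Switch = no.** Let p be the share of MIN-E patients who switch, and D the excess mean CCI of switched over non-switched MIN-E patients. Then

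mean(all MIN-E) = mean(non-switched MIN-E) + p × D,

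so

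non-switched MIN-E − all HYBRID-E = (as-randomised difference) − p × D.

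Inputs:
- p is about 5%. Section {11b} expects conversions below 5% in each group. The Fig. 1 caption moves 4 converted patients from the experimental arm into the as-treated HYBRID-E group: 4/76 = 5.3%.
- D is not given in the document. The range 10 to 40 is assumed.

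| D | Shift at p = 5% | Shift at p = 4/76 |
|---|---|---|
| 10 | 0.5 | 0.53 |
| 20 | 1.0 | 1.05 |
| 30 | 1.5 | 1.58 |
| 40 | 2.0 | 2.11 |

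The relevant difference is 10 points ({14}). For scale only, since the protocol specifies no subgroup test: take 64 HYBRID-E against 64 × 0.95 = 60.8 MIN-E patients with SD 20. The standard error is 20 × √(1/64 + 1/60.8) = 3.58. A two-sided 5% test with no true difference would reject in 5.2%, 5.9%, 7.0% and 8.6% of trials for D = 10, 20, 30 and 40.

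**ERAS adherence.** Under no treatment effect, the within-subgroup contrast is distorted when adherence depends on both complications and arm. An illustration uses CCI with mean 30 and SD 20, and log-odds of adherence falling by 1 per SD of CCI. With adherence 50% in both arms, the spurious difference is near zero (0.03 and 0.06 points). With 50% in HYBRID-E against 60% or 70% in MIN-E, it is 1.6 to 3.6 points in both strata, here to the disadvantage of MIN-E. All these adherence inputs are hypothetical.

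**Platform.** The estimand's treatment definition lets HYBRID-E be robotic in the abdomen only, while MIN-E can be robotic in the abdomen, the thorax or both. The label therefore means different things in the two arms, whenever the choice is made.

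**The case against.** The strongest reply is that nothing confirmatory is touched. The primary model keeps converted patients in their randomised arm, the estimand treats switching by treatment policy, and the subgroups carry no alpha, test or decision rule. Section {20b} does not say how the switch variable enters an analysis, and {11b} says reasons for conversion are captured to evaluate converted patients further. That is compatible with plain description. This stands, and it limits the severity. It does not rescue the listing: as a treatment-effect subgroup the variable cannot work, and as a description it does not belong in that list.

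A reader might infer more than the documents support in five places.

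- **A switching share of 8/76 = 10.5%.** The caption excludes 8 converted patients from as-treated MIN-E but adds only 4 to HYBRID-E. A conversion in the abdominal phase is not a switch to HYBRID-E. With the figure not shown and conversions expected below 5%, this share is not supported.
- **A certain bias towards MIN-E.** The direction needs D > 0. The stated reasons for conversion make that plausible, but no value is given.
- **A platform chosen after allocation.** Section {11b} says the set-up differs, not when the platform is chosen. Section {11a} points to local standard and randomisation is stratified by centre. If platform follows centre, it acts largely as a baseline factor.
- **A known ERAS mechanism.** The article does not define the items, their timing or the yes/no threshold. Dependence on arm and complications is possible, not documented.
- **A mediator-adjusted model.** The phrase in {11d} is loose, but no stated model adjusts for perioperative care. The primary model contains treatment, age and centre.

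**Conclusion.** The point holds as a should-fix matter. The empty control cell in the switch subgroup follows from the design alone. The accompanying no-switch contrast differs from the as-randomised one by p × D, about 0.5 to 2 CCI points at roughly 5% switching if D lies between 10 and 40. That is small against 10 and rests on an assumed D. ERAS adherence is not a baseline factor, and the size of any distortion cannot be derived from the article. The platform subgroup is affected in the same way only if the choice follows allocation, but its unequal meaning across arms remains. The primary mITT comparison is sound on this point.

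**What to change.** - Remove switching from the list of treatment-effect subgroups. Report converted patients, with reasons and CCI, in a descriptive table.
- Replace ERAS adherence by a variable fixed before randomisation, such as whether the site runs an ERAS programme, or report adherence descriptively by arm.
- Define the platform subgroup by the intended platform recorded before randomisation, or by centre standard, and state which operative phase it refers to in each arm.
- Assess the remaining subgroups by a treatment-by-subgroup interaction.
- In {11d}, say that perioperative care is recorded for description by arm, in line with the model in {20a}.

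A complier-average estimate, dividing the mITT difference by the share completed as allocated, is not a suitable replacement. It assumes that allocation does not affect the outcome of converted patients, which is doubtful after an attempted minimally invasive procedure.

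The cost is SAP wording, before the SAP is finalised ahead of database closure, and one pre-randomisation eCRF field for the intended platform. For patients already enrolled, that field would have to be filled from the operating plan.

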#### Patient-reported outcome measures (PROM)

12.Overall pain at rest and during movement (Numeric Rating Scale, NRS) at visits 3–5. The NRS ranges from 0 “no pain” to 10 “pain as bad as you can imagine” or “worst pain imaginable”.13.Assessment of postoperative thoracic pain syndrome measured as pain in the chest at rest and while coughing (NRS, 0–10) at visits 3–10. Chronic postoperative thoracic pain syndrome is a common and debilitating complication after thoracic surgery and was thus included as an endpoint in our trial. HYBRID-E and MIN-E might have different rates of thoracic pain syndrome due to differences in surgical access.14.Quality of recovery according to QoR-15 at visits 3–5 [25]15.Quality of life measured via QLQ-C30 and QLQ-OES18 at visits 7–10

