### Participant timeline {13}

**Table Tabb:** 

**Visit**	**V1**	**V2**	**V3**–**5**	**V6**	**V7**	**V8**	**V9/V10**
	Before surgery	Surgery (day 0)	POD 2 (+1) POD 4 (+1) POD 7 (+2)	Discharge	POD 30 (±5)	POD 90 (±5)	12 months postop. 24 months postop.
	**Outpatient/inpatient**	**Inpatient**			**Outpatient**	**Outpatient or telephone/mail**	
Eligibility criteria	X						
Informed consent	X						
Baseline demographics and clinical data	X						
Randomization	X						
Surgical data		X					
Histopathology (lymph node count, R0-rate)		X					
Assessment of primary endpoint (CCI)			X	X	X		
Assessment of reoperations			X	X	X	X	X
Safety (SAE)			X	X	X	X	
Assessment of secondary, oesophagectomy-specific outcomes according to ECCG			X	X	X		
Length of hospital stay				X			
Pain at rest and during movement (NRS)			X				
Thoracic pain syndrome measured as pain in the chest at rest and while coughing (NRS)			X	X	X	X	X
Quality of recovery (QoR-15)	X		X				
Health-related quality of life (EORTC QLQ-C30 + OES-18)	X				X	X	X
Disease-free survival					X	X	X
Overall survival (including 90-day mortality)		X	X	X	X	X	X

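### QoR-15 and QLQ scores are collected before surgery, but the stated secondary-endpoint model names no baseline score, so intervals for these outcomes will be wider than needed

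*Protocol article*

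**What the plan says.** Under the heading on additional analyses {20b}, the protocol article gives one generic model for secondary endpoints: "regression models including the treatment group as the fixed effect and centre as random effect as specified for the primary endpoint will be used". Only the survival outcomes are handled by other methods.

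The model it points to, under statistical methods {20a}, is a "linear mixed model including treatment group and adjusting for age as a fixed effect, as well as center as a random effect". It was written for one CCI value per patient. On covariance the article adds: "The correlation matrix will have a variance components structure".

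The patient-reported outcomes are repeated. The outcomes section lists "Quality of recovery according to QoR-15 at visits 3–5" and "Quality of life measured via QLQ-C30 and QLQ-OES18 at visits 7–10". The participant timeline {13} also marks V1, before surgery, in the QoR-15 row and in the EORTC QLQ-C30 and OES-18 row. Neither pain row is marked at V1.

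For baseline data, section {20b} says that "all baseline values will be evaluated descriptively per group and for the whole cohort". It states no other use. Missing values of secondary endpoints are not imputed.

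**The concern.** The trial asks patients to complete QoR-15 and the QLQ questionnaires before surgery, and the stated model then does not use the answers. For a continuous score, the patient's own earlier value is often the strongest available predictor of the later one. Leaving it out puts between-patient variation that could have been explained into the residual.

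What is at stake is precision. The trial is sized for the CCI alone, so the width of the intervals for quality of recovery and quality of life is whatever 128 or so analysable patients happen to give. A covariate that is already being collected narrows them without recruiting anyone.

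There is a second, conditional matter. The generic model was built for one value per patient, while these outcomes have three to eight. The article does not say whether visits are analysed separately or together. If they were put together under that model unchanged, nothing in it would account for rows from the same patient.

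**Working it through.** **The plan's own figure.** Sample size {14} uses a CCI difference of 10 and an SD of 20, so a standardised difference of 0.5. A two-sided t-test at 5% with 80% power needs 63.8, so 64 per group and 128 in all (power at 64 per group is 80.1%). Allowing for 15% loss, 64 / 0.85 = 75.3, so 76 per group and 152 in all. Both figures reproduce. The article states no figure for any patient-reported outcome.

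**Inputs from the outcomes section and the participant timeline**

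| Outcome | V1 value | Later visits | Number |
|---|---|---|---|
| QoR-15 | yes | V3–V5 | 3 |
| QLQ-C30/OES18 | yes | V7–V10 | 4 |
| Overall pain (NRS) | no | V3–V5 | 3 |
| Thoracic pain (NRS) | no | V3–V10 | 8 |

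The article gives no correlation for any of these scores. Those below are assumptions, shown as ranges.

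**Step 1: adding the V1 score.** Let ρ be the correlation between V1 and follow-up scores, given the terms already in the model. Adjustment multiplies the residual variance by 1 − ρ² and the interval width by √(1 − ρ²). The equivalent number of unadjusted patients is 128 / (1 − ρ²).

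| ρ (assumed) | Variance factor | Width factor | 128 adjusted patients are worth |
|---|---|---|---|
| 0.3 | 0.91 | 0.954 | 141 |
| 0.5 | 0.75 | 0.866 | 171 |
| 0.6 | 0.64 | 0.800 | 200 |

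Variance falls by 9% to 36% and interval width by about 5% to 20% over 0.3 to 0.6. The factors do not depend on the number of patients. The last column does, and fewer than 128 may answer at later visits.

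**Step 2: are the unadjusted intervals valid?** With one visit per fit there is one row per patient, which is the situation the primary model was made for. A simulation with 64 patients per arm, 8 centres (entered as fixed effects for speed) and 3,000 runs per setting gave coverage of 94% to 96% for nominal 95% intervals. So they are valid.

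**Step 3: what if visits were stacked with no patient term?** With m visits and within-patient correlation r, the true variance is 1 + (m − 1)r times the one the model reports. Coverage is then 2Φ(1.96 / √(1 + (m − 1)r)) − 1.

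| m | r = 0.3 | r = 0.5 | r = 0.7 |
|---|---|---|---|
| 3 (QoR-15, overall pain) | 88% | 83% | 79% |
| 4 (QLQ) | 84% | 78% | 73% |
| 8 (thoracic pain) | 73% | 64% | 58% |

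Simulation agrees to within about two percentage points (56% in the last cell). This step describes a hazard to be excluded. The article does not say that it will be done.

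**The case against.** The strongest reply is that outcome-specific covariates and visit structure belong in the statistical analysis plan, which the article says will be finished before database closure and which is not shown. That stands for visit terms and covariance structure, on which the article is silent. It weighs less for the baseline score: the article states a model and states what baseline values are for, and an analysis plan that follows both would leave the V1 score out.

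A reader might infer several stronger things that the article does not support:

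- **That the model is closed, with treatment and centre alone.** The wording is open as to further covariates, and the reference to the primary model plausibly brings in age. A descriptive summary of baseline values does not forbid their use as covariates.
- **That the confidence intervals will be false.** No sentence says visits are pooled as independent rows. Outcomes defined at listed visits fit per-visit comparisons equally well, and those have correct coverage.
- **That chance baseline imbalance biases the comparison.** Under randomisation it does not. The unadjusted interval already allows for it, and the loss is one of precision.
- **That one repeated-measures model is mandatory.** It can use a patient's other visits when one is missed, and it is compatible with no imputation. But an unstructured covariance over eight visits has 8 × 9 / 2 = 36 parameters. Late QLQ visits are also cut off by death: the introduction puts 3-year survival at about 50% for resectable patients, and a model treating missed visits as ignorable would extrapolate past death. The choice can be left to the trial team.

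**Conclusion.** The point holds as a matter of precision. As written, the secondary-endpoint model names no baseline score for two instruments that are measured at baseline. The cost is intervals whose variance is 1.10 to 1.56 times that of an adjusted analysis (1 / 0.91 to 1 / 0.64), for an assumed correlation of 0.3 to 0.6. The true correlation is unknown and may differ between the first postoperative days and 24 months, so the gain may differ by visit.

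The point covers QoR-15 and QLQ-C30/OES18 only. For all four repeated outcomes a safeguard is worth stating: visits are not to be combined without a patient-level term. The consequence is modest, because these endpoints are secondary and reported descriptively with intervals. The confirmatory CCI test and the 128/152 sample size are untouched.

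**What to change.** State, in the protocol or the analysis plan, that:

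1. The models for QoR-15, QLQ-C30 and QLQ-OES18 include the V1 score as a covariate, alongside treatment, age and centre. The pain scales keep the model without a baseline score.
2. The treatment difference is reported per visit. This can come from separate models at each visit, or from one model with visit, treatment-by-visit and a within-patient covariance.
3. If visits are combined, a patient-level term or covariance is required. The primary-endpoint model is not to be applied to stacked visits as it stands.
4. A rule applies when the V1 score is missing, since without imputation a patient lacking it would drop out of the adjusted model.

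The cost is wording and model code. The V1 questionnaires are already scheduled, so no visit, form or patient is added.
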